## Abstract

**Background:**

Previous research shows that providing social support in socioevaluative stress situations reduces participants’ stress responses. This stress-buffer effect, however, does not hold for everybody, and some studies even found a stress-amplifying effect of social support. Motive disposition research suggests that social motives (affiliation and power) lead to differential and sometimes even opposing affective and physiological responses to interpersonal interaction processes. We here integrate both lines of research and hypothesize that participants with strong affiliation motives benefit, while participants with strong power motives do not benefit from social support in terms of psychobiological responses to a given stressor. Further, participants with strong affiliation and power motives are expected to respond to social support with the arousal of motive-specific affects and reproductive hormone responses (affiliation: progesterone; power: estradiol and testosterone). In addition, we test sex differences in the response to social support and in the strengths of social motives.

**Objective:**

The main objective of this study is to test whether social motives and participants’ sex moderate the effects of social support in stressful situations.

**Methods:**

We aim to collect data from 308 participants recruited at our local university. Participants’ social motives are assessed using a standardized measure in motive research (Picture Story Exercise). Then, the Trier Social Stress Test for Groups (TSST-G) is used to experimentally induce psychosocial stress. One group of participants receives social support from an associate of the experimenter, while the control group does not receive social support. Stress responses will be assessed by a modified version of the state anxiety scale of the State–Trait Anxiety Inventory and by physiological indicators of stress (cortisol and α-amylase from saliva samples) at 7 measurement points. Reproductive hormones will be analyzed in 4 of these 7 saliva samples. Heart rate and heart rate variability will be assessed continuously. We will additionally measure participants’ performance in an interview (part of the TSST-G) using a self-developed categorization system.

**Results:**

The Ethics Committee of the University of Constance approved the application to conduct the study on December 18, 2018. Furthermore, the study was retrospectively registered in the German Clinical Trials Register (DKRS; ID: DRKS00028503) on March 09, 2022. The start of the experiment was planned for the beginning of 2019, but was postponed to June 2021 due to COVID-19. Publication of the first results is planned for spring 2023.

**Conclusions:**

Our theory-driven integration of social motives in social support research and the precise analysis of sex differences might disentangle inconsistent findings in TSST research. The more faceted view on individual differences has direct implications for applied contexts as it provides a framework for tailored conceptualizations of social support programs.

**Trial Registration:**

German Clinical Trials Register DRKS00028503; https://tinyurl.com/5a87x4da

**International Registered Report Identifier (IRRID):**

PRR1-10.2196/39509

## Introduction

### Stress and Social Support

There is an extended body of research outlining that stress affects basically every physiological system [1,2] and significantly impairs subjective well-being [3,4]. Therefore, it is unsurprising that the World Health Organization anticipates stress-related illness to progress to the second leading cause of disease in the coming decades [5]. Hence, it is essential to better understand the complexity of the concept of stress to be able to develop effective interventions. In the last decades, a great deal of research has shown that social support, defined as “social interactions or relationships that provide individuals with actual assistance or with a feeling of attachment to a person or group that is perceived as loving or caring” [6], can improve health [7-10]. One of the leading explanations for this phenomenon is that social support has a stress-buffering effect [11,12] and can thus counteract the negative consequences of stress. For example, social support leads to lower mortality rates [13,14], and better recovery from surgery [15] and sport injuries [16]. Yet, interestingly social support does not work as a stress buffer for everyone [8]. We assume that social support is perceived differently by individuals and investigate social motives (affiliation and power motive) [17] as moderators. They influence the perception of interpersonal relationships and should therefore also explain responses to social support.

### Implicit Motives

Implicit motives are preferences for certain kinds of incentives and disincentives, which modulate reward experiences [17-21]. Being relatively stable across time (such as personality traits), they drive, orient, and select behaviors for summaries [22]. Motive research has focused on the 3 domains of affiliation, power, and achievement motives, of which, we consider only social motives in our study. 

Individuals with a strong affiliation motive derive pleasure from affiliative experiences [17,23]. They have the desire for warm and friendly interpersonal relations [24], aim to feel socially related, want to experience reciprocal care and concern for important others [17,25], and emotionally suffer from discord, rejection, and loneliness [17,25,26]. Situations in which these needs can be satisfied lead to an affiliation motive–specific affect, such as joy, and feeling socially related [27].

Individuals with a strong power motive have the desire to have an impact on others and influence others (in socially desirable and undesirable ways) in order to feel superior to others and gain or maintain reputation and prestige [28,29]. Simultaneously, they aim to avoid defeat, other’s dominance, and feelings of inferiority [30]. In brief, they have “the capacity to derive pleasure from having physical, mental, or emotional impact on other individuals or groups of individuals and to experience the impact of others on themselves as aversive” [17]. The lack of opportunities in which others can be impacted or, even worse, situations signaling one’s inferiority function as stressors and lead to a power motive–specific affect (eg, feeling inferior and experiencing limited control) and impaired well-being [31,32]. 

Social motives are also associated with specific hormones [33,34]. Being inferior, for example, in a contest situation, has been associated with a decrease in testosterone in men with strong power motives [35]. For high power–motivated women, motive frustration leads to a decrease in estradiol [35]. Arousal of the affiliation motive is accompanied by an increase in progesterone for both sexes [33,36,37]. Furthermore, social motives in relationship with stress have been associated with various parameters of health, including blood pressure and the immune system [20], medication use and somatic symptoms [38], or job burnout and physical symptoms [39]. In summary, previous research has confirmed that affiliation and power motives lead to differential emotional, behavioral, and physiological responses to social cues. 

### Social Support and Social Motives

Based on the evidence that both social support and social motives modulate the stress response, we aim to investigate to what extent the interplay of these 2 factors can contribute to further enlightenment of the stress-buffer effect. Social support situations are highly ambiguous, leaving wide room for interpretation about, for example, one’s position in the social context, the intentions of the social support provider, and the quality of social relationships. By this, they are prototypes of social interaction processes, which are full of incentives or disincentives for social motives. They can, however, be perceived very differently by individuals with strong affiliation in contrast to power motives and therefore elicit different physiological and psychological responses. Thus, social support might signal a positive and warm relationship for individuals with a strong affiliation motive, but trigger feelings of weakness and inferiority in individuals with a strong power motive. In summary, we assume that social motives influence the perception of social support provided by others and function as a stress buffer in affiliation-motivated individuals and as a stress amplifier in power-motivated individuals.

### Social Support, Sex, and Gender

Other moderators that are discussed to influence participants’ responses to social support are sex and gender [8,40,41]. Women benefit stronger in terms of well-being from being socially supported than men [42,43], even though some studies found opposite effects [44]. Thus, the empirical evidence on whether and how women and men differ in their responses to social support is inconsistent. 

Sex differences have also been found in social motive research. Since the arousal of the affiliation and power motives in a specific situation is accompanied by the release of female reproductive hormones (estradiol and progesterone) and a male reproductive hormone (testosterone), it is assumed that this sex specificity should also be reflected in corresponding motive differences. Women are expected to show higher scores in affiliation motives, and men are assumed to have higher power motives. This was clearly empirically supported for the affiliation motive [45,46], whereas for the power motive, the result pattern is less clear [45,47]. These motives are assumed to correlate with a concept on a broader level of abstraction, that is, gender role self-concept (GRSC) [48]. The individual GRSC is defined as describing oneself with agentic traits like confident or assertive (masculine GRSC) versus with communal traits like empathic or cooperative (feminine GRSC). We assume that the inconsistent findings reported above may be due to shared variance among sex, GRSC, and motives. We aim to identify the specific influences of sex, GRSC, and social motives on the stress response to social support by considering them simultaneously and disentangling them in our statistical analyses.

### Planned Research

The main objective of this study is to test whether social motives and participants’ sex moderate the effects of social support in stressful situations. We use the Trier Social Stress Test for Groups (TSST-G) [49] that is based on the Trier Social Stress Test (TSST) [50], which is an established stress-induction paradigm triggering strong psychobiological stress responses [51]. Schultheiss et al [52] found that the TSST elicited differently strong cortisol responses for individuals with weak and strong implicit achievement motives, which supports our assumption that the TSST might be a potentially suitable paradigm that reveals motive differences. Wiemers et al [53] concluded from their study that the TSST has a specific arousal effect for the implicit power motive.

This study varies from classic TSST studies in the following aspects. While TSST studies usually focus on the detection of the stress hormone cortisol [54,55], we add the analysis of reproductive hormones (progesterone, estradiol, and testosterone), which will allow us to examine the arousal of motives in social support situations. We will further extend the TSST paradigm by analyzing participants’ responses in an interview (part of the TSST) to obtain an indicator for speech performance. While in the classical TSST paradigm, it is only announced that speech will be recorded (as an additional stressor), we here will actually record speech and apply a simple evaluation system to assess speech performance as a variable that we assume depends on stress.

Except for these variations, we will adhere to the procedure of the TSST-G [49]. As in previous studies analyzing social support [40,41,56], the experimental group will receive social support during the TSST preparation phase. The control group will also be exposed to stress but will not receive social support. To test the study hypotheses (see below), self-reports (well-being, perceived stress, and motive-specific affect) and biological parameters (heart rate, heart rate variability, cortisol, and reproductive hormones) will be collected (Figure 1).

**Figure 1 figure1:**
[figure not shown]
Trier Social Stress Test for groups (TSST-G): Phases of the procedure.

### Objectives

We will test the below hypotheses to investigate the role of social motives in the social support and stress relationship.

#### Hypothesis 1: Effect of Stress Induction Hypothesis

Participants in both groups (social support vs no social support) show an increase in stress responses comparable to that in previous studies. We expect a rise in the physiological parameter cortisol by at least 1.5 nmol/mL (Miller criterion) [57].

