#### Salivary Cortisol

The concentration of cortisol in saliva will be recorded in ng/mL. Seven saliva samples will be collected using Salicaps (IBL International) at measurement time points T0 (−11 min before the TSST-G), T1 (TSST-G onset), T2 (after the job interview), T3 (after the arithmetic task), and T4, T5, and T6 during the resting phase (+30 min, +45 min, and +65 min, respectively, after TSST-G onset). Cortisol will be determined with the Cortisol free in Saliva ELISA assay from Demeditec.

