### Statistical Analysis

Statistical analysis will be performed using IBM SPSS Statistics, Version 28 (IBM Corp) for Windows (statistical analysis and graphs). We will perform an analysis of variance with repeated measures to determine if the TSST procedure results in significant increases in psychological and biological variables for all participants. We will calculate multiple linear regressions to examine interaction effects. In these regressions, we will first include the control variables, then the condition as a dummy variable, and finally the individual predictors and their interaction terms. To account for repeated measurements of the collected hormones, the area under the curve with respect to increase will be calculated and used as a dependent variable [71]. As an additional effort to ensure that participants with a delayed significant increase in their hormones will not be excluded, an adjusted increase value will be calculated, regardless of the time of measurement. This value will be obtained by subtracting the baseline value from the peak value. Multiple regressions will be calculated again with these adjusted values. Nonbiological dependent variables, such as those obtained from the psychological test battery, will be added as means. Only data from individuals who have fully completed the TSST protocol will be included in the final analyses. Missing data will be added by multiple imputation.

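### The minimum cortisol rise in Hypothesis 1 is printed in a unit that puts it at about 544 ng/mL on the recorded scale, and the planned test never applies it

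*Protocol article*

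**What the plan says.** Hypothesis 1 in the protocol article has two parts. The first is general: "Participants in both groups (social support vs no social support) show an increase in stress responses comparable to that in previous studies". The second gives a figure and ties it to a named, cited criterion (the Miller criterion): "We expect a rise in the physiological parameter cortisol by at least 1.5 nmol/mL".

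The Salivary Cortisol section fixes the scale of the data: "The concentration of cortisol in saliva will be recorded in ng/mL". It also names the method: "Cortisol will be determined with the Cortisol free in Saliva ELISA assay from Demeditec". Neither section converts between molar and mass units.

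Statistical Analysis plans a repeated-measures analysis of variance "to determine if the TSST procedure results in significant increases in psychological and biological variables for all participants". The figure of 1.5 does not reappear there. The same section defines a baseline-to-peak difference for the hormones, but assigns it only to the regressions: "This value will be obtained by subtracting the baseline value from the peak value. Multiple regressions will be calculated again with these adjusted values".

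**The concern.** A threshold in a formal hypothesis has to be usable on the data that will be collected. Here the threshold is an amount of substance per millilitre and the data are a mass per millilitre. The two are linked only by the molar mass of cortisol, and the conversion yields a value far above what a saliva assay read in ng/mL would be expected to return.

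The second difficulty is logical. The hypothesis states a rise of at least a fixed amount, whereas the planned test asks whether there is a significant increase. A significant time effect is compatible with a mean rise well below the stated minimum, so the test and the claim do not match.

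What is at stake is the evidence that the stress procedure worked in this sample. The Discussion acknowledges that there is no unstressed comparison group, so the within-study rise in stress markers is the only direct evidence of induction the study will produce. A reader who tries to judge that rise against the printed criterion will find that it cannot be applied.

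**Working it through.** **Inputs from the protocol article**

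- Threshold: 1.5 nmol/mL (Hypothesis 1).
- Recorded unit: ng/mL (Salivary Cortisol).
- Planned test: repeated-measures ANOVA for a significant increase, with no threshold (Statistical Analysis).

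**Assumptions, not in the document**

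- Molar mass of cortisol, C21H30O5, from atomic weights: 21 × 12.011 + 30 × 1.008 + 5 × 15.999 = 362.466 g/mol, which is the same number in ng/nmol.
- Salivary cortisol peak: 5 to 100 ng/mL, with the upper end chosen to be generous.

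The threshold is taken from a cited source and not derived in the article, so there is no calculation of the authors' to reproduce. The check is a unit conversion.

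**Step 1. Threshold as printed.** Concentration in ng/mL = concentration in nmol/mL × molar mass:

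1.5 × 362.466 = 543.7 ng/mL (equivalently 1,500 nmol/L).

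**Step 2. Threshold if the volume unit were the litre.**

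1.5 × 362.466 / 1,000 = 0.544 ng/mL.

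The two readings differ by a factor of 1,000.

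**Step 3. Can the printed value be reached?** A rise from baseline cannot exceed the peak itself. The required rise divided by the whole assumed peak is:

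| Assumed peak (ng/mL) | 543.7 / peak |
|---|---|
| 5 | 109 |
| 10 | 54 |
| 20 | 27 |
| 50 | 11 |
| 100 | 5.4 |

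The ratio stays above 5 throughout, so the conclusion does not depend on where in the range the true peak lies. The per-litre value of 0.544 ng/mL would be attainable over the same range.

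**Step 4. Does the planned test address the minimum?** Write d for the true mean rise in ng/mL and c for the threshold in ng/mL. The ANOVA addresses whether there is a rise, that is, d > 0. Hypothesis 1 states d ≥ c, or that individual rises are at least c; the text does not say which. Rejecting d = 0 does not establish either form for any c above zero. The quantity needed, peak minus baseline, is already to be computed, but no planned step compares it with c.

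**The case against.** The strongest reply is that this is probably a one-letter slip beside a named and cited criterion. An analyst would go to that source, and the printed value is so far out of range that nobody would apply it unnoticed. That is fair as to cause and likely harm, and it argues against the highest severity. It does not remove the error: the figure stands in a formal hypothesis, it is the only numerical cortisol criterion in the article, and the recorded unit gives the reader no way to recover the intended value.

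A second reply is that no planned analysis uses the figure. This also stands, and it rules out several stronger readings that a reader might infer:

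- *That nobody would be a responder and Hypothesis 1 would therefore fail.* The article plans no responder classification and sets no decision rule on the figure. It states an expectation.
- *That every later hypothesis rests on the threshold.* The regressions for Hypotheses 2 to 5 are not conditional on it, and the Discussion justifies omitting an unstressed group by the established record of the procedure, not by this criterion.
- *That the bare number 1.5 would be applied to the ng/mL data.* This would be a third threshold, 1.5 / 362.466 × 1,000 = 4.14 nmol/L, or 2.8 times a per-litre reading. Nothing in the article suggests that anyone intends it.
- *That the ANOVA ignores the groups.* The phrase "results in significant increases in psychological and biological variables for all participants" can equally mean that an increase is expected in both arms. Study Design makes experimental group a between-subject factor, and the exact model terms are detail that an article may leave to the analysis plan.

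Finally, the claim that the printed threshold is unattainable needs a salivary range that the article does not give. The size of the excess depends on the assumed ceiling; the direction does not change anywhere in the range tried.

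**Conclusion.** The point holds in two limited parts. First, the threshold is wrong as written for data in ng/mL: it converts to about 544 ng/mL, against 0.54 ng/mL if per litre was meant. This rests on an assumed molar mass of about 362.5 g/mol. That it could not be met rests on an assumed peak of no more than 100 ng/mL, at which the required rise is still 5.4 times the whole peak. Which unit the cited criterion uses cannot be settled from the article.

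Second, a significant increase in the ANOVA would support the general part of Hypothesis 1 but not its stated minimum.

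The damage is to how the stress-induction check is judged and reported. Estimates and tests for Hypotheses 2 to 5 are unaffected. Severity: should-fix.

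**What to change.** 1. Check the unit in the cited criterion and correct Hypothesis 1. State the threshold in ng/mL, the scale of the recorded data, with the conversion shown. If the source says 1.5 nmol/L, this is 0.54 ng/mL.
2. Say whether the minimum refers to each participant's rise or to the group mean.
3. Alongside the ANOVA, report for each experimental group the already planned baseline-to-peak cortisol rise against the corrected threshold: the mean rise with its confidence interval, and the proportion of participants who meet the threshold.

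The cost is one corrected unit and one descriptive table. No new data are needed, and the regression models and sample size stay as they are.

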#### Hypothesis 2: Social Support × Social Motive Hypothesis

The affiliation motive moderates the effects of social support on stress responses. A higher affiliation motive of participants is associated with greater benefit from social support, that is, they will express lower psychobiological stress responses (better self-reported well-being, less perceived stress, lower heart rate, higher heart rate variability, and lower levels of cortisol and α-amylase). While the affiliation motive is expected to function as a stress buffer, the power motive is assumed to function as a stress amplifier. A higher power motive of participants is associated with greater negative impact from social support, that is, they will report lower well-being, more perceived stress, higher heart rate, lower heart rate variability, and higher levels of cortisol and α-amylase.

#### Hypothesis 3: Motive-Specific Arousal Hypothesis 

Participants with strong affiliation and power motives respond to social support with arousal of self-reported motive-specific affect (ie, affiliation: joy and feeling socially related; power: feeling weak and inferior) and with an increase in motive-specific reproductive hormone responses* *(affiliation: progesterone; power: estradiol and testosterone).

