#### Hypothesis 4: Sex Difference Hypothesis

Women and men are hypothesized to differ in their social motives, with higher affiliation and lower power motives in women than in men. Women and men will specifically respond to social support with relative increases in estradiol and progesterone in women and testosterone in men.

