## Discussion

The aim of this study is to investigate whether social motives and participants’ sex moderate the effect of social support in stressful situations. We expect that participants with a strong affiliation motive will benefit from social support in terms of reduced psychobiological stress responses when being critically evaluated by others. For those participants, social support is supposed to serve as a stress buffer. In contrast, social support is expected to act as a stress amplifier in participants with a high-power motive, resulting in higher psychobiological stress responses.

To elucidate the influence of implicit social motives on affect in specific situations, we will record participants’ motive-specific affect. We postulate that participants with a high affiliation motive, will respond to social support with affiliation and an increase in progesterone. Participants with a high power motive will show feelings of inferiority and a decrease in testosterone or estradiol.

To explore the influence of implicit motives without bias, we also consider sex as a variable in our study. It is hypothesized that males exhibit a higher power motive and females exhibit a higher affiliation motive. This is expected to be reflected in motive-specific hormones.

Some studies have shown that social support has positive effects [72], while others have reported no, small, or adverse effects of social support [73,74]. With the introduction of implicit motives as moderator variables, as well as taking sex into account, we strive to explain why people react differently in same situations. Through this person-situation approach, we enable a more differentiated view on the effect of social support in stress situations. In summary, with this sophisticated view, we aim to provide a foundation that interventions could be designed in an individualized way and therefore only produce positive effects and no adverse effects.

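### Hypothesis 3 predicts a rise in testosterone and estradiol for power-motivated participants given support, the Discussion predicts a fall, and the analysis fixes no sign

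*Protocol article*

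**What the plan says.** Hypothesis 3 (Objectives) concerns how participants with strong social motives respond to social support. For the power motive, the predicted affect is "power: feeling weak and inferior". The same sentence goes on "and with an increase in motive-specific reproductive hormone responses", and lists estradiol and testosterone as the hormones for power and progesterone as the hormone for affiliation.

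The Discussion restates the expectation: "Participants with a high power motive will show feelings of inferiority and a decrease in testosterone or estradiol".

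The background appears in three places in the Introduction:
- Implicit Motives: being inferior "has been associated with a decrease in testosterone in men with strong power motives", and "For high power–motivated women, motive frustration leads to a decrease in estradiol".
- Social Support and Social Motives: support may "trigger feelings of weakness and inferiority in individuals with a strong power motive".
- Social Support, Sex, and Gender: "the arousal of the affiliation and power motives in a specific situation is accompanied by the release of female reproductive hormones", a sentence that goes on to include testosterone.

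The Abstract names the hormones without a direction. The Statistical Analysis section plans multiple linear regressions for the interactions. The hormone outcomes are the area under the curve with respect to increase (AUCi) and, as a second analysis, peak minus baseline. It states no expected sign for the motive-by-support coefficient.

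**The concern.** The article gives opposite directions for the same participants, hormones and exposure. Hypothesis 3 also joins a state of inferiority to a hormone rise, although the only evidence the article cites on inferiority or frustration in power-motivated people is a fall.

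The power-by-support coefficient for testosterone and estradiol is the biological half of the power arm of Hypothesis 3. A positive coefficient would agree with the listed hypothesis and a negative one with the Discussion. With no sign fixed in the analysis section, the label of confirmed or contradicted can be settled once the estimate is known. The study was registered retrospectively, so the published protocol is an important public record of what was predicted.

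**Working it through.** The article gives no figure to reproduce. The main check is to set its statements side by side.

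**Affiliation arm, for comparison.** Implicit Motives, Hypothesis 3 and the Discussion all give an increase in progesterone. This also bears on how Hypothesis 3 should be read. One clause covers progesterone, estradiol and testosterone. Since it means a rise for progesterone, it cannot comfortably mean a change of either sign for the other two.

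**Power arm.**

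| Place | Direction for testosterone and estradiol |
|---|---|
| Implicit Motives, men | down (testosterone, under inferiority) |
| Implicit Motives, women | down (estradiol, under frustration) |
| Social Support and Social Motives | none stated; support triggers inferiority, the state linked above to a fall |
| Social Support, Sex, and Gender | up (motive arousal in general) |
| Hypothesis 3 | up |
| Discussion | down |
| Abstract | none |
| Statistical Analysis | none |

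Hypothesis 3 and the Discussion conflict directly. The Introduction leans towards a decrease but contains both lines of reasoning.

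**Size, as illustration.** Alpha and sidedness are assumed, because the Statistical Analysis section gives neither. For one hormone with no true effect, a two-sided test at level α gives a false confirmation with probability α/2 if one sign counts, and α if either does.
- α = 0.05: 0.05/2 = 0.025 against 0.05.
- α = 0.10: 0.10/2 = 0.05 against 0.10.

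The ratio is 2 at any α.

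**Whether the outcomes can show a fall.** Reproductive hormones are sampled at −11, 0, +20 and +65 minutes, so the intervals are 11, 20 and 45 minutes (76 in total). Taking the first sample as baseline, a sustained change d from the second sample onwards gives AUCi per minute = d × (11/2 + 20 + 45)/76 = d × 70.5/76 = 0.93d. A drop of 1 within-person SD gives −0.93 SD. A simulation (400,000 draws, independent standard normal noise at the four times) gave the same value.

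For peak minus baseline, the same simulation gave:
- Baseline sample may be the peak: mean +1.03 SD with no change and +0.42 SD after a true drop of 1 SD. The measure was never negative. The shift is 0.42 − 1.03, about −0.6 SD.
- Peak taken after baseline only: mean +0.84 SD with no change and −0.16 SD after the drop. The shift is −0.16 − 0.84 = −1.00 SD.

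The article does not say which version is meant. Under the first, a fall is shrunk and cannot appear as a negative value. Under the second, a uniform fall does carry through to a comparison between participants, but the value itself is offset upwards by noise.

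**The case against.** The strongest reply is that the Objectives section says the listed hypotheses are the ones to be tested. Hypothesis 3 names one direction there, so the Discussion sentence could be treated as loose prose. A reader might go further and infer that the plan accepts either sign, or that the hypothesis cannot be refuted. The document does not support that: nowhere does it say both signs count. What stands is narrower. Two directions are published, neither is tied to the coefficient, and the one in the formal hypothesis is the one that the cited evidence on inferiority does not favour.

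Four further limits are fair:
- The rationale is not one-sided. Hypothesis 3 is framed around motive arousal, and the Introduction links arousal to hormone release. The testosterone evidence comes from a contest situation, not from social support. The authors must choose and justify the sign; the Introduction does not settle it for them.
- A reader might see Hypothesis 4 as a further contradiction, since it says "Women and men will specifically respond to social support with relative increases in estradiol and progesterone in women and testosterone in men". That is an average response by sex. A rise on average and a negative power-by-support slope can both hold.
- A reader might combine the two hormones and compare 1 − 0.95² = 9.75% with 1 − 0.975² = 4.94%. That comparison assumes two independent tests, although the text may intend testosterone for men and estradiol for women. It also mixes in ordinary multiplicity. The sign conflict accounts only for the factor of two per test.
- A true effect would still be estimated with its sign. Only its label as confirming or contradicting is open, so the result is not arbitrary.

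**Conclusion.** The inconsistency is real and stands in current text. Hypothesis 3 and the Discussion predict opposite signs for testosterone and estradiol in power-motivated participants given support, and the analysis section does not resolve it. The consequence is room to choose the confirming direction afterwards, not evidence that this is intended.

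The scope is the hormone part of the power arm of Hypothesis 3. The progesterone prediction, the stress outcomes of Hypothesis 2, the allocation and the sample size are untouched. The size is a doubling of the false-confirmation chance per hormone if either sign were accepted: 2.5% to 5% at an assumed two-sided alpha of 0.05, and 5% to 10% at 0.10. The remarks on peak minus baseline rest on a simple noise model and matter only if a decrease is the chosen prediction.

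**What to change.** Before hormone data are analysed by arm:

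1. State and justify one predicted sign of the power-by-support coefficient for testosterone and one for estradiol, by sex if that is intended.
2. Make Hypothesis 3 and the Discussion agree. A decrease fits Implicit Motives, Social Support and Social Motives, and the existing Discussion sentence. If an increase is kept, explain why arousal should prevail over the cited evidence on inferiority.
3. State that a significant effect of the opposite sign will be reported as contradicting Hypothesis 3.
4. If a decrease is chosen, base the test on AUCi or on a signed change from baseline, since peak minus baseline is built to capture rises.
5. Leave Hypothesis 4 as it is, apart from clarifying that it concerns average responses by sex.

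The cost is rewording and, under a decrease, naming which planned hormone outcome carries the test. The only downside is that one of the two signs can no longer be claimed as support.
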